## Abstract

**Background:**

Anxiety disorder is the most prevalent psychiatric disorder. Benzodiazepines, which are often used for anxiety in patients with anxiety disorder, have various side effects. Lavender, one of the most commonly used essential oils in aromatherapy, has the potential to reduce benzodiazepine use for anxiety disorders.

**Methods:**

This study is a multicenter, double-masked, randomized, placebo-controlled clinical trial. The study will recruit patients aged 20–59 years old with generalized anxiety disorder and panic disorder among anxiety disorders. The bottle containing the test solution (lavender aroma essential oil or distilled water) will be given to the patients. Patients will carry the bottles with them in their daily life and use the drops on tissue paper when anxious. The primary endpoint is the number of times anxiolytics used in 28 days.

**Discussion:**

If the use of benzodiazepines could be reduced by sniffing lavender aroma, which is inexpensive and safe, it would contribute not only to the risks associated with benzodiazepine use but also to the health care economy and could even be added as a standard treatment.

**Trial registration:**

University hospital Medical Information Network Clinical Trials Registry (UMIN-CTR), ID: UMIN000034422 Registered 17 January 2019.

**Supplementary Information:**

The online version contains supplementary material available at 10.1186/s12906-023-04231-1.

## Background

Anxiety disorder is an extremely common mental disorder [1], and its frequency has increased over the last decade [2]. A meta-analysis conducted by Lijster et al. showed that 21.3 years is the average age at the onset of anxiety disorders [3]. In the European Study of the Epidemiology of Mental Disorders, an international epidemiological study conducted in Europe (Belgium, France, Germany, Italy, the Netherlands, and Spain) among people aged 18 years and older, the lifetime prevalence of anxiety disorders was 13.6% [4]. The World Mental Health Japan Survey, conducted among Japanese residents aged 20–75, reported a 10.8% lifetime prevalence of anxiety disorders [5]. Anxiety disorders have been found to contribute to increased rates of absenteeism in both work and educational settings, resulting in a greater financial burden when compared to other mental diseases [6]. According to the fifth version of Diagnostic and Statistical Manual of Mental Disorders (DSM)-5, major anxiety disorders that affect adults include generalized anxiety disorder (GAD), panic disorder (PD), social anxiety disorder (SAD), agoraphobia, and specific phobia [7].

The most common treatment for anxiety disorders is a combination of pharmacotherapies, including the use of benzodiazepines [8], serotonin reuptake inhibitors (SSRIs), serotonin-norepinephrine reuptake inhibitors [9], and psychotherapy (cognitive behavioral therapy) [10, 11]. Usually, patients with anxiety disorders use benzodiazepines for transient anxiety symptoms such as panic attacks. However, their prolonged use may have adverse health effects despite their short-term benefits. These factors encompass the potential for dependence and adverse outcomes, such as cognitive decline [12, 13].

Aromatherapy is one of the most extensively used supplementary therapies [14]. It is based on the therapeutic application of essential oils produced from aromatic herbs that can be ingested, applied topically to the skin, or inhaled [15]. Some essential oils have been known as anxiolytic candidates, namely lavender, also known as *Lavandula angustifolia* Mill. A randomized placebo-controlled study of 116 volunteers showed reduced stress levels in the group using lavender oil for aromatherapy compared with the placebo group [16]. In adults with GAD, the orally administered anxiolytic effect was comparable to that of benzodiazepines [17] and SSRIs [18], and fewer adverse effects were reported than with synthetic drugs.

The aforementioned research may suggest the possibility of aromatherapy as a treatment for anxiety disorders. However, these do not include studies of inhaling or sniffing essential oil. While inhaling essential oils changes moods in healthy volunteers [19], a study on women undergoing abortions indicates that aromatherapy cannot be substituted for anxiolytics [20]. Therefore, anxiolytic effects of inhaling essential oils still need to be elucidated. Additionally, it should be noted that inhaling and sniffing may exhibit different effects because inhaling essential oil means the oil is gas while sniffing means the oil can be in various forms, such as liquid or solid.

In summary, to the best of our knowledge, the possibility of chronic exposure to sniffed essential oil as an aromatherapy for treating anxiety disorders has never been evaluated. Therefore, the effect of sniffing fragrance in aromatherapy should be elucidated first before delving into which essential oils show an anxiolytic effect.

In this study, starting with lavender as our initial focus, we will investigate the efficacy and safety of sniffing lavender aroma in patients with anxiety disorders, aiming to develop a reliable and safe alternative and complementary treatment.

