### Primary endpoint

The primary outcome measure is the number of times anxiolytics were used within 28 days.

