### Statistical analysis

#### Analysis set

For the next analysis sets, statistical analysis will be done.Full analysis set (FAS)All patients will be regarded as FAS, with the exception of those who received care in flagrant violation of ethical standards, those who were not given the test solution, and those whose data for the key outcome were missing.Safety analysis set (SAS)The SAS will be referred to as the group of patients to whom the test solution was distributed.Per protocol set (PPS)The PPS will be referred to as the group of patients who fall under the FAS but do not match the criteria below.3-1.Patients who fail to satisfy the predetermined inclusion criteria or contravene the established exclusion criteria for this study3-2.Notable departures from the established study procedure3-3.Patients who had not carried a bottle containing the test solution for more than 20 days

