### Adverse events

The incidence of adverse events is minimal, and no discernible health or safety concerns have been reported in relation to the participants included in the clinical research. The safety monitoring group will oversee data monitoring. Throughout the course of the 1-week program, any small or significant occurrences related to the intervention or routine care groups will be observed. The chief investigator will review any negative or unexpected consequences.

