## Discussion

The objective of this study is to examine the effectiveness and safety of olfactory exposure to essential oil fragrance among individuals diagnosed with anxiety disorders, with the aim of establishing a dependable and secure alternative and adjunctive therapeutic approach for anxiety management in this population. Lavender was taken as a starting point for exploring the use of essential oil fragrances as potential anxiolytic treatments, because a systematic review of aromatherapy on anxiety clearly indicates that it is the major fragrance [28]. Considering this objective, the placebo should meet the following criteria: 1) Be indiscernible from its appearance, i.e., a colorless clear liquid; 2) Having no fragrances. Therefore, our placebo of distilled water is justified. In fact, a systematic review of lavender as a potential anxiolytic supports that using distilled water as a placebo is appropriate [29].

However, there are some limitations to be considered. First, it should be noted that secondary endpoints of STAI, SDS, GHQ60, and PSQI are subjective. Therefore, patients’ objective psychological states or sleep qualities, such as functional magnetic resonance imaging, heart rate variability, or polysomnography might strengthen our findings. Because these were not the primary endpoint, we do not perform further objective assessment. Second, the primary endpoint of the number of times anxiolytics used is not completely objective. Although the possibility may not be high, we should be cautious about the accuracy of patients’ reporting of their anxiolytics use.

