Last but not least, limitations of statistical analyses should be seriously discussed. The difference of primary endpoint in the mean frequency of benzodiazepine use between the distilled water group and the lavender aroma group of -10 ± 7.5 times/month was derived from a simple assumption. Therefore, we cannot deny the possibility of manipulating the sample size. Nonetheless, this assumption was based on our clinical experience of patients with mood disorders by the intervention of complementary medicine, such as mindfulness. Another statistical limitation lies in imputation. If missing values tend to appear in one common characteristic of patients, using imputation to handle such patients could reveal significant insights. However, because the sample size was calculated considering dropout rate of 30%, and such analysis can be performed separately, we decided to perform no imputation.

Considering aforementioned limitations, if the use of benzodiazepines could be reduced by sniffing inexpensive and safe essential oils, including lavender, this would contribute not only to the risks associated with benzodiazepine drug use, but also to the health care economy. In addition, since sniffing aromas is simpler than taking medications with drinking water, the use adherence is likely to be higher and it could be added as a standard treatment.

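### Safety is a stated aim, but no safety endpoint is listed, the safety set has no named analysis, the adverse-event text does not fit this trial, and "sniffing lavender aroma, which is inexpensive and safe" claims more than 15 lavender patients can show

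*Protocol article*

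**What the plan says.** The Background sets the aim: "we will investigate the efficacy and safety of sniffing lavender aroma in patients with anxiety disorders". The main Discussion repeats it: "The objective of this study is to examine the effectiveness and safety of olfactory exposure to essential oil fragrance".

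The endpoints concern efficacy or symptoms. Under Primary endpoint: "The primary outcome measure is the number of times anxiolytics were used within 28 days". The secondary endpoints are total anxiolytic amount, STAI, SDS, GHQ60, PSQI and the number of anxiety attacks.

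Under Analysis set, the article defines a safety population: "The SAS will be referred to as the group of patients to whom the test solution was distributed". That section opens with a general statement that the listed sets will be analysed. The sections that follow use the full analysis set for patient background and for the primary analysis, use the per-protocol set for sensitivity, and treat the secondary endpoints like the primary.

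The Adverse events section begins: "The incidence of adverse events is minimal, and no discernible health or safety concerns have been reported in relation to the participants" included in the research. It then describes observation over a one-week programme in intervention or routine-care groups, oversight by a safety monitoring group, and review by the chief investigator.

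The abstract's Discussion refers to "sniffing lavender aroma, which is inexpensive and safe". The main Discussion reasons from the condition "if the use of benzodiazepines could be reduced by sniffing inexpensive and safe essential oils, including lavender".

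**The concern.** An aim needs an outcome that can answer it. Here one of two stated aims has no listed outcome and no named analysis, and the text describing how harms are observed does not match the trial. Meanwhile the answer appears as a premise, in the word safe and in the statement that adverse events are minimal.

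The Background makes that premise harder to accept. The authors say that, to their knowledge, repeated sniffing of essential oil as a treatment for anxiety disorders has not been evaluated, and that inhaling and sniffing may act differently. The comparison of adverse effects that they cite concerns oral lavender.

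At stake is the safety conclusion, not the efficacy result. A report that follows the article could repeat that lavender is safe without a tabulated comparison behind it. Read literally, it could rest on harms observed for only part of the treatment period.

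**Working it through.** **1. Aim against endpoints and analyses**

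| Item | Where | Content |
|---|---|---|
| Aim | Background; Discussion | Efficacy and safety |
| Endpoints | Primary endpoint; Secondary endpoint | Anxiolytic use, symptom scales, sleep, anxiety attacks; no safety outcome |
| Population | Analysis set | Safety set: everyone given the solution |
| Named analyses | Summary between treatment groups; Primary endpoint; Secondary endpoints | Full analysis set and per-protocol set only |

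The endpoint list is not a short summary. It goes down to the PSQI components and the SDS cut-offs, so brevity is an unlikely reason for the missing safety outcome.

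**2. Adverse events section against the design**

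| Feature | Adverse events | Rest of the article |
|---|---|---|
| Observation period | One week | 28-day outcome period |
| Comparator | Routine care | Distilled-water placebo, double-masked |

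Read literally, the window covers 7/28 = 25% of the treatment period and names an arm that the trial does not have.

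**3. The plan's own sample size**

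Inputs from Sample size calculation: difference 10, SD 7.5, two-sided 5%, power 80%, dropout about 30%. The exact two-sample t-test has power 75.7% with 9 per group and 80.5% with 10 per group, so 10 are needed. Then 10/(1 − 0.30) = 14.3, rounded up to 15 per group and 30 in total. The stated figures reproduce. They rest on anxiolytic use alone.

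**4. What 15 lavender patients can show about harm**

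The safety set keeps everyone who was given the bottle, including later dropouts, so the denominator is 15 if the recruitment target is met.

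Exact upper limits for zero events in 15:
- one-sided 95%: 1 − 0.05^(1/15) = 0.181, or 18.1%
- two-sided 95%: 1 − 0.025^(1/15) = 0.218, or 21.8%

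Chance of seeing no event at all, (1 − p)^15. The article gives no event rates, so p is assumed:
- p = 1%: 0.99^15 = 0.86
- p = 5%: 0.95^15 = 0.463, or 46%
- p = 10%: 0.90^15 = 0.21

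Exposed patients needed to exclude a rate p when no event occurs (one-sided 95%), ln(0.05)/ln(1 − p) rounded up: 29 for 10%, 59 for 5%, 299 for 1%.

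Testing the arms against each other would add little. With no event in 15 placebo patients, 4 of 15 on lavender gives a Fisher exact p of 0.100 and 5 of 15 gives 0.042. Intervals are therefore more informative than a test.

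**The case against.** The best defence is that the article does deal with safety. It announces analysis for all listed sets, plans some observation of adverse events, and names a monitoring group. A condensed article may also leave adverse-event tables to a full protocol or SAP that is not shown. This stands in part. A reader might infer that safety is not assessed at all, or that the safety set is never used, and the text does not support that. Missing table detail would not be a finding. What remains is that no safety outcome is listed, that no named analysis is tied to the safety set, and that the one section describing observation contradicts the design.

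A reader might also infer that patients who stop early because of the scent vanish from the safety assessment, since the full analysis set drops those with no primary outcome. They do not: they stay in the safety set. For the same reason, limits computed on completers only would use the wrong denominator.

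It is also fair to say that sizing on efficacy alone is usual, and that the aims speak of investigating safety, not of proving it. Both points stand. The sample size is not the fault; the unqualified word safe is.

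Finally, the statement on minimal adverse events could be a status report from a trial dated 2018 to 2024, and the remarks in the Discussion are conditional. The Discussion's direct argument for adding sniffing to standard treatment is ease of use and likely adherence. That reading is possible. But the statement gives no count, arm or source, so it cannot stand as a result, and safe still enters the argument as a given.

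**Conclusion.** The point holds as a mismatch between aim, endpoints, safety text and claim. Safety is a stated aim with no listed endpoint and no named analysis on the safety set. The adverse-event section conflicts with the 28-day, placebo-controlled design and states its result in advance. Safe is asserted where the Background says evidence on this route is lacking.

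A clean record in 15 lavender patients would exclude only event rates above about 18% to 22%, over at most 15 × 28 = 420 patient-days of treatment. These limits assume that all 15 receive the bottle and that every event is captured; the 46% chance of missing an event altogether also assumes a true rate of 5%. The efficacy analysis is unaffected. The change is worth making because it is cheap and determines what the trial may conclude about safety.

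**What to change.** 1. List a descriptive safety endpoint under Secondary endpoint: patients with at least one adverse event, and patients who discontinue because of one, from distribution of the bottle through the 28-day period. Report both by arm on the safety analysis set with exact 95% confidence intervals, without a formal test.
2. In Adverse events, remove the statement that incidence is minimal, and reconcile the observation window and group names with the 28-day placebo design.
3. In the abstract and the main Discussion, replace safe with a statement limited to short-term tolerability. Say that zero events in 15 lavender patients would exclude only rates above 18.1% (one-sided) or 21.8% (two-sided).

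The cost is protocol wording and one table. Data management describes REDCap as supporting adverse-event reporting. The diary described under Interventions covers only medication and aroma use, so an adverse-event form may have to be added if none exists. The downside is a more modest safety claim.

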## Design

### Study design

This study is a multicenter, double-blind, randomized, and placebo-controlled clinical trial. To compare the effectiveness of treatment with lavender aroma, we will compare two groups of patients: a lavender aroma group and a non-lavender aroma group who were provided with a placebo. Double masking is necessary due to the possibility of changes in medical treatment once the researcher knows the allocation results.

### Patients

The study will include patients aged 20–59 with GAD and PD among anxiety disorders diagnosed using the DSM-5. The study dates ranged between September 9, 2018, and March 31, 2024. Posters and other methods will be for study recruitment. We will explain everything using permission from the explanatory paper and consent forms, and we will obtain everyone’s signed consent. Written informed consent will be obtained from all the participants. Moreover, participants can withdraw at anytime after participating in this study.

#### Inclusion criteria

Patients must satisfy the following requirements:Only female patients aged 20–59 who consented to the study.Patients who were diagnosed with GAD or PD using the DSM-5.Patients who have taken anxiolytics more than seven times within the past month.Patients with no history of aroma use.

#### Basis for setting inclusion criteria

The patient’s age was defined as the age when the patient consented to the study. The effectiveness of the aroma may differ according to sex. To detect efficacy efficiently, the study needed to be limited to a more homogeneous population and was therefore limited to female patients only.Patients with GAD and PD were chosen as they are most frequently encountered in daily practice.We included patients who took anxiolytics because we expected these patients to benefit from the treatment.Patients who had never used aroma-related products were chosen to eliminate the possibility that a history of aroma use influenced this study.

#### Exclusion criteria

Patients who fell into the following criteria below are excluded from the study.Patients who are diagnosed with significant physical and mental health issues by the physician in charge.Patients who are pregnant, possibly pregnant, within 28 days postpartum, or are breastfeeding.Patients who are diagnosed with any olfactory dysfunction or chronic nasal obstruction.Patients with dilated thoughts of death.Patients using anxiolytics other than benzodiazepines as an abortive medication for anxiety attacks.Any patients deemed ineligible by the principal investigator or sub-investigator for this study were excluded.

#### Basis for setting exclusion criteria

The above criteria in points 1, 4, and 6 were used to ensure the general safety of the patients.

Point 2 was established because the safety of the patient treatment for pregnant women, fetuses, and newborns was not established.

Points 3 and 5 were established to exclude patients who would be affected by the evaluation of the treatment under study.

### Interventions

The study schedule is depicted in Fig. 1. After obtaining the 4-week baseline benzodiazepine medication status and other information, the patients will be assigned to either the aromatherapy or distilled water (placebo) groups. The patient will begin carrying the bottle immediately after the outpatient visit, and in this study, carrying is defined as carrying the bottle at all times in a bag or similar while going out. However, for the time spent at home, the patient is considered to be carrying the bottle because the test solution is always available if the patient experienced anxiety attacks.

**Fig. 1 Fig1:**
[figure not shown]
Flowchart of the study schedule. GAD = generalized anxiety disorder; PD = panic disorder; STAI = State Trait Anxiety Inventory; SDS = Self-Rating Depression Scale; GHQ60 = General Health Questionnaire 60; PSQI = Pittsburgh Sleep Quality Index

Lavender aroma (*L. angustifolia* ssp. Angustifolia (Pranarom International, Ghislenghien, Belgium) or distilled water is used as the test solution, which is stored in a 10 ml glass bottle with a drop stopper (Pranarom International). The bottle containing the test solution (lavender aroma essential oil or distilled water) will be given to the patient without informing them of the type of test solution. Patients will be asked to carry the bottles with them daily at all times and use the drops on the tissue paper when anxious. The patients will be instructed to maintain a diary in which they will record details on their benzodiazepine medication and aroma usage (Supplementary Fig. 1).

### Data management

The study data will be collected and stored in the Research Electronic Data Capture system (REDCap), a web-based, secure, Health Insurance Portability and Accountability Act-compliant research management platform [21, 22], which is also an electronic data capture system for electronically gathering clinical data in clinical research. This system provides comprehensive support for various research procedures, encompassing patient scheduling, patient randomization, data entry and management, data safety monitoring, and adverse event reporting. One of the main advantages of REDCap is that it requires a thorough audit trial. The individual providing the input is also immediately alerted if any field is blank or values outside the acceptable range are entered. Backup paper copies were given when internet connectivity was lost, and these copies were then entered into REDCap.

The study database will not contain any personal identifiers, such as names or other information that might potentially lead to the direct identification of a patient by a third party; instead, the enrolled patients’ data were accessed and queried using the REDCap software. To prevent unauthorized access, the datasets saved on computers are password-protected and encrypted. Patients will be identified by numbers or symbols, and the relationship between these and details that may be used to quickly identify a person (such as name or address) to a third party will not be maintained during data collection. It is necessary to maintain a record of the correspondence between information that is clearly identifiable to a third party (such as name and address) in a locked cabinet (personal information manager: HA).

